### Data codes

Data codes are available in online supplementary appendix 1 (available at our website https://rsjh.ca/[name]/CES-AC_Protocol_Appendices_Jun29_16.pdf).

### Follow-up

Outcomes will be counted in a follow-up window to 24 months postindex prescription, death, exit from BC or the end of the study window. We will censor follow-up for death or departure from the province, but not clinical outcomes, in order to gather information on the clustering of important clinical events (eg, patient has a bleed, discontinues warfarin, then has a vascular event and dies).

### Analysis plan

The primary analysis will be intention-to-treat, meaning that if the index prescription is for warfarin, then any outcome events are attributed to warfarin whether switching occurs or not. This mimics the conservative, recommended analysis in clinical trials. However, this approach may underestimate benefit and harm, therefore a secondary ‘as-treated’ analysis will explore outcomes based on actual treatment during follow-up. Although both analyses occur after baseline confounders are adjusted for, the as-treated analysis requires further adjustments for measured time-varying confounding and selection bias using inverse-probability weighting.^34^ Switching between anticoagulants will be further explored by examining comparative duration on each anticoagulant as well as switch frequency.

For the main analysis, the effects of treatment with the use of DOACs versus warfarin will be estimated from time-to-event models (Cox proportional hazards or Poisson). Risk modifying effects such as age, sex, dose and risk factors (including congestive heart failure, hypertension, diabetes, prior stroke, prior major bleed, renal or liver failure, interacting concomitant medications, alcohol abuse) will be evaluated using tests of interaction. Tests of interaction will be used to identify key subgroups in which warfarin may be better than DOACs or DOACs better than warfarin, using the two coprimary outcomes and net clinical benefit as defined above. Models can simultaneously control for potential confounders such as cardiovascular disease, rural/remote location of residence, physician practice—all estimated at index date (further details in online supplementary appendix 1). Sample size is unlikely to allow individual DOAC versus DOAC comparison, but outcomes will be tabulated by individual drug.

Community-based outcome event rates and the RE-LY trial suggest a coprimary outcome event rate of ∼12% per year for warfarin versus 10% per year for DOACs.^3^
^35^ Assuming conservatively that accrual extends over 3 years and that patients have a minimum of 1 year of follow-up, and that 67% of the sample is on warfarin, an analysis based on outcomes at 1 year would require 6000 patients on warfarin and 3000 patients on DOACs for 80% power. Since our analysis will be time-to-event rather than using binary outcomes at 1 year, we expect to have greater power than estimated.

Missing data, including missing laboratory results, are represented as variables in the propensity score. All analyses will be carried out using SAS. 95% CIs for the estimates will be calculated, with two-tailed, p<0.05 considered significant. Absolute risk difference and NNT to benefit or harm will be calculated. Analysis and reporting will be compliant with Strengthening the Reporting of Observational Studies in Epidemiology (STROBE) recommendations.^36^

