Our primary objectives for this study are as follows: (1) to clarify the overall comparative effectiveness and safety of DOACs versus warfarin in clinical practice where high quality is expected, (2) to compare and contrast our results with the relevant phase III randomised trials and (3) to identify the key predictors of superior effectiveness and safety (which drug is better for which patients) in vulnerable populations—predictors which are very likely to include INR control quality in the warfarin patients, remote location (probable lack of ready access to INR testing), access to certain specialists and presence of severe renal impairment.

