### Control for confounding

New users of DOACs are likely to differ in several characteristics from new users of warfarin. We expect them to be younger and with less comorbidity. To control for confounding, we will adjust estimates by age, sex and propensity score. Propensity scores will be computed by multiple logistic regression of the logit of the conditional probability of allocation to warfarin versus any DOAC (conditional on patient being a new user of either anticoagulant) regressed on potential confounders at baseline. Among the variables considered will be sex, dose, CHADS_2_ (Congestive heart failure, hypertension, age, diabetes, stroke - 2 points) score, and HAS-BLED score (hypertension, abnormal renal or hepatic function, previous stroke, bleeding, labile INR, age, drugs/alcohol), other vascular events, concomitant medications, drug plan coverage, remote location, neighbourhood income quintile, physician specialty, haemoglobin and year of cohort entry. We plan to evaluate conventional and high-dimensional propensity scores, the latter estimated using preselected and empirically chosen variables from medication, hospital and medical services data.^37^

Analyses of switching patterns, including the duration of OAC exposure and the switching frequency, will be treated as time-dependent confounders and controlled by marginal structural modelling.^38^

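### The only propensity score described is fitted to all new users, so the interaction tests meant to show which drug suits which patients can be confounded if drug choice works differently inside a subgroup

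*Protocol article*

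**What the plan says.** The Introduction lists three primary objectives. The third is to find the predictors of which drug is better for which patients. It expects these to include INR control, "remote location (probable lack of ready access to INR testing"), access to specialists and severe renal impairment.

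The Analysis plan turns this into a method: "Tests of interaction will be used to identify key subgroups in which warfarin may be better than DOACs or DOACs better than warfarin", using both coprimary outcomes and net clinical benefit. The listed modifiers include age, sex, dose, heart failure, diabetes, prior stroke, prior major bleed, and renal or liver failure. Significance is "two-tailed, p<0.05 considered significant".

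Under Control for confounding, estimates are adjusted for age, sex and a propensity score. The score is a logistic model for the "conditional probability of allocation to warfarin versus any DOAC (conditional on patient being a new user of either anticoagulant"). Conventional and high-dimensional versions will be evaluated. No other baseline score is described. The Analysis plan allows further confounders in the outcome models but does not fix this. The strengths and limitations list speaks of matching, whereas Control for confounding speaks of adjustment.

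**The concern.** A propensity score balances the arms in the population for which its model is right. Fitted to everyone, it gives each covariate one effect on drug choice, unless subgroup terms are added. If a covariate pushes drug choice differently inside a subgroup, the arms can be balanced overall and unbalanced there. The treatment-by-subgroup term then mixes effect modification with confounding specific to that subgroup. More patients do not remove this, and an overall balance table need not show it. The result would be read as advice on which drug suits a vulnerable group.

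The text gives one concrete reason to look. The Introduction says DOACs are contraindicated in severe renal impairment, and renal failure is on the interaction list. The few such patients given a DOAC may well be selected differently from other DOAC users.

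**Working it through.** **The plan's own figure.** Inputs from the Analysis plan: "12% per year for warfarin versus 10% per year for DOACs", "67% of the sample is on warfarin", and the statement that the analysis "would require 6000 patients on warfarin and 3000 patients on DOACs for 80% power". With allocation 2:1, pooled p = (2 × 0.12 + 0.10)/3 = 0.1133, and

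n(warfarin) = [1.960·√(0.1133 × 0.8867 × 3) + 0.8416·√(0.12 × 0.88 + 2 × 0.10 × 0.90)]² / 0.02² = (1.0761 + 0.4498)²/0.0004 ≈ 5,822.

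That gives 2,911 on DOACs. With continuity correction it is 5,971 and 2,986. Power at 6,000 + 3,000 is 81.2%. The figure is reproduced, but it covers the overall comparison only. The plan gives no figure for the interactions, so the rest is simulation under assumed inputs.

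**The mechanism.** Assume no drug effect, a 15% subgroup, and two confounders with log hazard ratios of 0.4 and 0.3 per SD. The first confounder's coefficient for DOAC choice is −0.5 outside the subgroup and −0.25, 0 or +0.25 inside. After weighting by the whole-cohort score, the overall mean difference in that confounder is about 0.00 SD. Inside the subgroup it is 0.22, 0.44 and 0.65 SD. The implied false rate ratio is about exp(0.4 × difference):

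- exp(0.088) = 1.09
- exp(0.176) = 1.19
- exp(0.260) = 1.30

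Fine stratification on the same score, standing in for matching, gave 1.10, 1.21 and 1.32.

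**The score as a covariate.** The true ratio of rate ratios is 1.00 throughout.

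| Setting (assumed) | Whole-cohort score | Modifier-specific score |
|---|---|---|
| 20% subgroup, rate ratio 10/12; DOAC use differs only in level or not at all | 0.96 to 1.00 | 0.95 to 1.00 |
| Same, but one of two coefficients zero / doubled / reversed in the subgroup | 1.00 / 1.04 / 1.08 (SE about 0.03) | 0.99 / 1.04 / 0.99 |
| 15% subgroup, no drug effect; confounders push drug choice the same way | 1.00 to 1.03 | 1.00 to 1.03 |
| Same, pushing opposite ways | 1.07 / 1.19 / 1.24 (SE 0.02) | 1.00 to 1.03 |
| 15% subgroup, age also adjusted; same way | 0.94 to 1.06 (SE about 0.04) | 0.93 to 1.10 (both directions) |
| Same, opposite ways | 1.15 to 1.18 (SE about 0.04) | as above |

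The dependence on direction has a simple explanation. If the confounders that steer drug choice also raise risk in the same proportions, the score is close to a prognostic index, and adjusting for it removes most of the confounding even where the score is wrong. If they steer in opposite directions, it is not.

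In the reversed case of the second row:

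- Adding only a separate slope for the whole-cohort score left the ratio at 1.08.
- Adding the covariates themselves to the outcome model brought it to 1.00.

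**Weighting by the whole-cohort score.** The run with age adjusted gave 1.11 to 1.29. With a single confounder whose coefficient was zero, doubled or reversed in the subgroup, weighting gave 1.26, 0.80 and 1.62. With equal coefficients it gave 0.97 to 0.99.

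**What this means at the planned size.** In the second-row setting the log interaction had SE 0.027 at 400,000 patients, so at 9,000 it is 0.027 × √(400,000/9,000) = 0.18.

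- A false ratio of 1.08 lies ln(1.08)/0.18 = 0.43 SE from zero. It would be declared significant in about 7% of studies (8.5% simulated, SE 2 points).
- A ratio of 1.18 lies 0.92 SE away and would be declared in about 15%.

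On the effect scale, 0.833 × 1.08 = 0.90 and 0.833 × 1.18 = 0.98.

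**The case against.** A reader might infer that the protocol itself says prescribing follows different rules in these subgroups, so that bias is certain. The text does not support that. The Introduction names remote location, specialist access and renal impairment as predictors of outcome. Remote location and specialist access are not on the interaction list. The renal contraindication, and the expectation that DOAC users are younger with less comorbidity, describe how often DOACs are chosen. A whole-cohort score containing those variables can model that, and the simulations with a difference in level alone showed no detectable problem.

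Three further points are fair:

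- An article may leave the form of the score and the balance checks to a fuller plan or to its appendix, and nothing here rules out subgroup terms.
- Weighting is planned for the secondary as-treated analysis. The primary method is adjustment, so the weighting figures show what could happen and not what is planned.
- Age and sex are adjusted for as well, and further covariates are permitted. Adding the covariates removed the bias in the reversed case.

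These points limit the size and certainty of the concern. They do not remove it. Permission to add covariates is not a commitment, and the score described for the interaction tests is defined for the whole cohort. Matching is mentioned too, so the use of the score that is more exposed to this bias is not excluded.

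**Conclusion.** The point holds in a conditional form. A whole-cohort score can produce a false answer on which drug is better for a subgroup if covariate effects on drug choice differ inside that subgroup. The document does not state that they do. It makes this plausible for renal failure.

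With the score as covariate, the false interaction ranges from negligible to roughly 15 to 20%, with one extreme setting at 1.24. It is larger with weighting or with stratification on the score. At about 9,000 patients the inflation of false-positive tests under adjustment is modest, but the bias remains while the standard error shrinks in a larger cohort.

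Subgroup sizes, coefficients and outcome effects are all assumptions. Some settings were run only once, with SE about 0.04, and there the modifier-specific score itself ranged from 0.93 to 1.10, so the figures show order of magnitude only. The overall DOAC versus warfarin comparison and its sample size are not affected.

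**What to change.** For the interaction analyses, state the following:

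- The score is estimated with modifier-by-covariate terms, or separately within modifier levels where numbers allow.
- The outcome model lets the slope of that score differ by level.
- Covariate balance and overlap are tabulated within each level before outcomes are examined, with particular attention to renal failure.
- Where balance is not reached, the outcome model is adjusted for the unbalanced covariates and the interaction is presented as potentially confounded.

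Say in the same place whether the score enters as a covariate or through matching, because the size of the problem depends on it.

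The cost is more analysis work and slightly wider intervals in small subgroups. The sample size does not change.

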### Control for confounding

New users of DOACs are likely to differ in several characteristics from new users of warfarin. We expect them to be younger and with less comorbidity. To control for confounding, we will adjust estimates by age, sex and propensity score. Propensity scores will be computed by multiple logistic regression of the logit of the conditional probability of allocation to warfarin versus any DOAC (conditional on patient being a new user of either anticoagulant) regressed on potential confounders at baseline. Among the variables considered will be sex, dose, CHADS_2_ (Congestive heart failure, hypertension, age, diabetes, stroke - 2 points) score, and HAS-BLED score (hypertension, abnormal renal or hepatic function, previous stroke, bleeding, labile INR, age, drugs/alcohol), other vascular events, concomitant medications, drug plan coverage, remote location, neighbourhood income quintile, physician specialty, haemoglobin and year of cohort entry. We plan to evaluate conventional and high-dimensional propensity scores, the latter estimated using preselected and empirically chosen variables from medication, hospital and medical services data.^37^

Analyses of switching patterns, including the duration of OAC exposure and the switching frequency, will be treated as time-dependent confounders and controlled by marginal structural modelling.^38^

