## Introduction

Comparative effectiveness research (CER) priorities of the Institute of Medicine have highlighted the treatment of atrial fibrillation and the comparative effectiveness of anticoagulants as priority topics.^1^ This is because of the widespread use of oral anticoagulants (OAC), particularly in elderly populations, their major benefit in preventing morbid and fatal thrombotic events and their potential for major harm, which is largely bleeding. Large rigorous randomised trials have been critical to allowing direct acting oral anticoagulants (DOACs) on to the market, but have not settled whether their rapid uptake in clinical practice, probable use in patient groups beyond those included in the trials, and use in countries where international normalised ratio (INR) monitoring is relatively high quality generates similar benefits and harms compared to warfarin.^2–5^

Currently more than 7 million prescriptions are dispensed annually for OACs in Canada.^6^ Warfarin is one of the most cost-effective medications in current use, with a 68% reduction in stroke rates and a significant decrease in all-cause mortality in atrial fibrillation, at a negligible drug cost.^7^ Warfarin's narrow therapeutic index, the variability of its effect in some patients and concern regarding drug and food interactions mandate laboratory INR monitoring of its anticoagulant effect.^7^ The need for monitoring and dose adjustment is reassuring to some patients and is the ‘gold standard’ adherence check for drugs, but burdensome for other patients and for physicians. The DOACs are given in fixed doses and do not require (or benefit from) INR monitoring. Three of these, dabigatran, rivaroxaban and apixaban, are now available in Canada. Within a year of dabigatran launch in 2010, worldwide sales were estimated at US$1 billion annually.^8^ However, by 2011 the Institute for Safe Medication Practices (ISMP) and the Food and Drug Administration (FDA) noted that dabigatran was the leading cause of drug-related serious harm and death reported to the FDA in 2011.^9^
^10^

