### Study cohort

The source population includes all BC residents aged 18 years or older, an estimated 3.6 million individuals. Our access to BC data includes de-identified data extracts from PharmaNet, Medical Services Plan billings (physician payments), the hospital Discharge Abstract Database (DAD), BC Vital Statistics death records and LifeLabs laboratory data. All data are accessed once appropriate approvals and payment are received, using Population Data BC secure research servers.^21^ Our sampling frame will be BC residents enrolled with the Medical Services Plan during the 12 months before starting an anticoagulant drug (index prescription). Eligibility for inclusion in the cohort will be those with a diagnosis of atrial fibrillation in hospital or medical services data within the 36 months prior to the index prescription.

Anticoagulant exposure will be determined from dispensed prescription database records, beginning 1 October 2010 and continuing until study end (details in figure 1). New users of warfarin, dabigatran, rivaroxaban and apixaban will be identified. To identify new users, a look-back observation period of 12 months prior to the index prescription date will be used and must indicate no anticoagulant use during this period. The index date will be defined as date of the new prescription for OAC. Determination of exposure, as far as possible, will be blinded to patient outcome.

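### Dose is a candidate propensity-score variable, although it is set with the index drug and has no scale common to warfarin and the DOACs

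*Protocol article*

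**What the plan says.** The protocol's Control for confounding section describes a logistic model for the "conditional probability of allocation to warfarin versus any DOAC", "regressed on potential confounders at baseline". The candidate list follows: "Among the variables considered will be sex, dose", then CHADS2, HAS-BLED, concomitant medications, location, income, physician specialty, haemoglobin and year of entry. HAS-BLED is spelled out item by item and includes "previous stroke, bleeding, labile INR, age, drugs/alcohol". Conventional and high-dimensional versions of the score are both to be evaluated.

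Four other statements bear on this:
- Study cohort: the 12-month look-back before the index prescription "must indicate no anticoagulant use during this period".
- Introduction: "The DOACs are given in fixed doses and do not require (or benefit from) INR monitoring". It also says that each DOAC has its own dosages, which vary with age and risk factors, and that warfarin is adjusted against the INR.
- Analysis plan: tests of interaction will cover "Risk modifying effects such as age, sex, dose and risk factors".
- Analysis plan: missing laboratory results enter the score as variables.

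**The concern.** A propensity score should predict which drug a patient receives from what was known before the choice. Dose fails this test. It comes into being with the dispensing that defines the exposure, and its numerical value depends on which drug was dispensed. Using it to predict the drug is partly circular, because the score starts to identify the arm and stops summarising baseline risk. Patients who were comparable before treatment then receive different scores, and overlap and precision fall. With some codings the estimate also moves. The score carries the confounding control for both coprimary outcomes.

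The same lack of a common scale makes dose uninterpretable as a modifier of the DOAC-versus-warfarin effect, although there it does no damage to the score.

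Labile INR raises a smaller, related question. A patient just starting an anticoagulant has, with few exceptions, no current on-treatment INR series from which to score it.

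**Working it through.** **1. The plan's own figure.** The article gives no figure for covariate choice. Its only relevant numbers are those of the design: 12% versus 10% at 1 year, 6000 warfarin and 3000 DOAC patients, two-sided 0.05, 80% power. With r = 0.5 and pooled p = (0.12 + 0.5 × 0.10)/1.5 = 0.1133, the number on warfarin is

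[1.960 × √(3 × 0.1133 × 0.8867) + 0.842 × √(0.12 × 0.88 + 2 × 0.10 × 0.90)]² / 0.02² = 5822,

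or 5971 with continuity correction. Power at 6000 + 3000 is 81.2%. The figure reproduces. It contains no covariate adjustment, so the fix leaves it unchanged.

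**2. Is dose a baseline variable?** The score is restricted to baseline confounders. A new user has had no anticoagulant for 12 months, so there is no current anticoagulant dose before index. The dose first exists on the index date, as an attribute of the drug dispensed. By the Introduction's account, DOAC doses are fixed and drug-specific while warfarin is titrated, so no scale is common to the arms.

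**3. What inclusion would cost (illustration; every input below is an assumption).** There were 100 replicates of N = 9000, about two thirds on warfarin.
- Warfarin choice: logit = 0.62 + 0.35 × age + 0.4 × comorbidity.
- Dose: warfarin mean 5, SD 2 mg/day, limited to 1–15. Three equally frequent DOACs at 300 or 220, 20 or 15, and 10 or 5 mg/day, the lower value being likelier with age.
- Labile INR: 35% of warfarin patients, after index, adding 0.6 to the log hazard.
- Analysis: Poisson model for the event on treatment, score quintile and age. RR is DOAC:warfarin.

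| Score contains | AUC | Score in 0.1–0.9 | RR | SE of log RR |
|---|---|---|---|---|
| Baseline variables only | 0.609 | 100% | 0.788 | 0.067 |
| + raw mg/day | 0.947 | 74.2% | 0.781 | 0.109 |
| + log mg/day | 0.950 | 27.1% | 0.785 | 0.108 |
| + reduced-dose flag (0 for warfarin) | 0.763 | 85.9% | 0.818 | 0.075 |
| HAS-BLED sum with post-index labile INR | 0.678 | 97.0% | 0.842 | 0.068 |
| Post-index labile INR as a separate item | 0.746 | 76.4% | 0.997 | 0.074 |

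Information kept is (0.067/0.109)² = 0.38 for raw dose, (0.067/0.108)² = 0.38 for log dose and (0.067/0.075)² = 0.80 for the flag.

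As a rough translation, 81.2% power corresponds to 0.885 + 1.960 = 2.845 standard errors. If the same loss applied to the planned design:
- raw dose: 2.845 × √0.378 − 1.960 = −0.21, or about 42% power;
- flag: 2.845 × √0.798 − 1.960 = 0.58, or about 72% power.

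**4. Labile INR.** If the baseline restriction is applied, the item is zero or missing for nearly everyone, and the result is the first row of the table: RR 0.79, no change. If it were scored from INRs after index, RR would move to 0.84 inside the HAS-BLED sum. The share of the log effect removed is 1 − ln(0.842)/ln(0.788) = 1 − 0.172/0.238 = 28%. A second simulation with similar inputs (35% labile, rate × 1.8, logit score as covariate) moved the warfarin:DOAC ratio from 1.295 to 1.142, a share of 1 − 0.133/0.259 = 49%. In both, nearly all of warfarin's excess risk runs through labile INR by construction: 0.65 + 0.35 × 1.8 = 1.28.

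**The case against.** **The list names candidates, and the appendix is not shown.** This is fair. Dose is to be considered, not fixed as included, and its coding may be set out elsewhere. But the objection is to what the text names: no coding turns an attribute of the index prescription into a baseline confounder, and all three codings tried did some harm.

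**Dose carries confounder information.** DOAC doses depend on age and risk factors, so a reduced dose partly marks frailty. This is true within the DOAC arm. The underlying factors can enter the score directly, through age, HAS-BLED items and laboratory values, without importing the identity of the drug.

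**Dose might mean the dose of other medicines.** Concomitant medications are listed separately, both among the score candidates and among the effect modifiers, so this reading is unlikely.

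**A reader might infer that overlap vanishes and the contrast cannot be estimated.** The document does not support that. It would follow from a coding by drug and dose together, which the article does not propose. With raw mg/day the contrast was still estimated, at a large cost in precision.

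**A reader might also infer that labile INR adjusts away about half of warfarin's effect.** This does not stand either. The text restricts the score to baseline, and the item appears only where the HAS-BLED acronym is spelled out. Nothing says that INRs after index are used. The share removed depends on the assumed pathway. Nor is the direction certain: the Introduction's interval for major bleeding runs from 11 fewer to 6 more per 1000, and if DOACs bled more, the same adjustment would push the estimate away from no difference. It is also too strong to say that labile INR cannot exist at baseline, since a patient treated with warfarin more than 12 months earlier may have an older INR record.

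**Conclusion.** The point on dose holds. Naming it as a score candidate conflicts with the section's own restriction to baseline confounders, and following the list as written would weaken overlap, precision or bias control in the primary comparison. The size depends on coding. In the illustration it ranges from a modest loss with a small shift in the estimate (reduced-dose flag) to the loss of about 62% of the information (raw or log mg/day). These figures rest on assumed doses, allocation and risks; they show the kind of harm and do not predict it for this cohort. Dose in the interaction list is a lesser fault of interpretation.

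On labile INR only a safeguard is warranted. Under the stated baseline rule the item is harmless and almost empty. It would bias the comparison only if scored after index, which the article does not state. In that case the missing-result variables could mark the DOAC arm as well.

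**What to change.** 1. Delete dose from the propensity-score candidates, and exclude index-prescription attributes from the empirically chosen variables of the high-dimensional score.
2. Delete dose from the list of modifiers tested for the DOAC-versus-warfarin contrast. Report results by DOAC dose descriptively instead.
3. State that HAS-BLED is computed without the labile-INR item, and that every score variable, including indicators for missing laboratory results, is dated before the index dispensing and can be defined in both arms.

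The cost is a change of wording and minor programming. No new data are needed, and the stated 6000 + 3000 is unaffected.

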DOACs, especially dabigatran, are contraindicated in patients with severe renal impairment because of accumulating drug concentrations.^12^ Atrial fibrillation is primarily a disease of the elderly, older patients are vulnerable to rapid decline in renal function, and patients with renal impairment are at significantly higher risk of bleeding even without anticoagulation.DOACs have no marker (as the INR is for warfarin) for their effectiveness, safety or adherence. In addition, DOACs may produce more adverse symptoms (eg, dabigatran and gastrointestinal symptoms) than warfarin leading to undetected no-adherence. Finally, all DOACs have relatively short half-lives, and missed doses may have more impact on anticoagulation outcomes. While patient adherence is closely monitored in phase III clinical trials, monitoring in usual care is much more variable.Although antidotes are becoming available, their absence left no reliable way to stop DOAC-associated bleeding, and the antidotes will be very expensive and restricted to hospital settings.^13^ Patient monitoring and follow-up is less vigilant in clinical practice compared to clinical trials, thus the outcomes of bleeding may not be as favourable in usual practice.There are several DOACs available, each with separate dosages and dosing schedules depending on patient age and risk factors. Doses for atrial fibrillation differ from those for other indications. This will create confusion for prescribers, the vast majority of whom do not specialise in this area, and may lead to errors. Similarly, information on switching anticoagulants, bridging with DOACs, follow-up intervals, DOAC drug interactions, etc, is sparse.Time in therapeutic range (TTR) for INR is a good surrogate for warfarin safety and effectiveness.^14^ Study centres including Canadian centres, which maintained good average TTRs, saw no significant advantage to DOACs in clinical outcomes.^15^ It is unclear whether routine clinical practice maintains a good average TTR.

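### Dose of the index anticoagulant is listed as a candidate propensity-score predictor of warfarin versus DOAC, although it is an attribute of the drug chosen and not a baseline confounder

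*Protocol article*

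**What the plan says.** Control for confounding defines the score as a logistic model for "the conditional probability of allocation to warfarin versus any DOAC", "regressed on potential confounders at baseline". The list of predictors opens: "Among the variables considered will be sex, dose". It goes on to risk scores, concomitant medications, location, income, prescriber specialty and other items. The score then enters the comparison directly: "we will adjust estimates by age, sex and propensity score". Conventional and high-dimensional versions are both to be evaluated, the latter drawing partly on empirically chosen medication variables.

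Elsewhere in the article, dose always refers to the anticoagulants:

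- Introduction, on the new drugs: "The DOACs are given in fixed doses".
- Introduction, on differences among them: "each with separate dosages and dosing schedules depending on patient age and risk factors".
- Introduction, on warfarin: "The need for monitoring and dose adjustment is reassuring to some patients".
- Analysis plan, as a subgroup factor: "Risk modifying effects such as age, sex, dose and risk factors".

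**The concern.** A propensity score should condition on what was known before the treatment choice. The index dose is decided with the drug, and for warfarin it is adjusted afterwards under INR monitoring. It is part of the exposure, not a cause of it.

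The practical risk is overlap. Doses of different drugs are not on a common scale, so an absolute dose carries information about which drug was dispensed. A score that contains it may predict treatment very well for reasons unrelated to confounding. With regression adjustment, the score then becomes nearly collinear with treatment: the standard error grows and the estimate leans on model form where the arms do not overlap. With matching, which the article's strengths and limitations box mentions, patients without counterparts are lost. The score supports the primary DOAC-versus-warfarin comparison, so the point bears on the main result.

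**Working it through.** **Step 1: what dose refers to.** Concomitant medications are a separate item in the same list, so it is not their dose. Study cohort requires no anticoagulant use in the 12 months before the index prescription, so it is not an earlier anticoagulant dose. Every other mention concerns the study anticoagulants. The remaining reading is the dose of the index anticoagulant.

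**Step 2: the plan's own figure.** Analysis plan gives 6000 warfarin and 3000 DOAC patients for 80% power, at 12% versus 10%, two-sided 5%. With r = 0.5 and pooled proportion (0.12 + 0.5 × 0.10)/1.5 = 0.1133:

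n(warfarin) = [1.960 × √(3 × 0.1133 × 0.8867) + 0.842 × √(0.12 × 0.88 + 0.10 × 0.90/0.5)]² / 0.02² = (1.076 + 0.450)² / 0.0004, which gives 5822, with 2911 on DOACs.

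A continuity correction gives 5971 + 2986. Power at 6000 + 3000 is 81.2%. The figure reproduces. It does not depend on this point; it supplies n = 9000 for the next step and makes no allowance for lost overlap.

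**Step 3: effect of dose on the score.** All inputs except n and the rough 2:1 split are assumptions, not document figures.

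- One simulated cohort of 9000 with five independent standard normal covariates.
- logit P(DOAC) = −0.75 − 0.4x₁ + 0.3x₂ − 0.3x₃ + 0.2x₄ + 0.3x₅, which gave 34.3% on DOACs.
- mg values drawn at random within arm, purely to illustrate scales. Disjoint: DOAC 10, 20, 150, 220, 300; warfarin 2, 2.5, 3, 4, 5, 7.5. Partly overlapping: DOAC 5, 10, 15, 20, 220, 300; warfarin 1, 2, 2.5, 3, 4, 5, 6, 7.5, 10. Both mg runs use log mg.
- Reduced-dose flag with probability 1/(1 + exp(1.2 − 0.6x₁)).
- Logistic score with a very small ridge term (0.001), so that it stays finite under separation.
- Common support: scores between the larger of the two arm minima and the smaller of the two arm maxima.

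| Dose term in the score | c-statistic | In common support |
|---|---|---|
| None | 0.67 | 8977/9000 (99.7%) |
| mg, disjoint scales | 1.00 | 0/9000 (0%) |
| Categories of mg strength, two values shared | 0.97 | 2377/9000 (26%) |
| mg, partly overlapping scales | 0.94 | 5265/9000 (59%) |
| Reduced-dose flag, 0 for all warfarin | 0.75 | 8343/9000 (93%) |
| Relative reduced-dose flag, both arms | 0.67 | 8976/9000 (99.7%) |

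A plausibility check on the strength row: only the values 5 and 10 occur in both arms. Expected numbers there are 3088 × 2/6 = 1029 DOAC and 5912 × 2/9 = 1314 warfarin, together 2343, close to 2377. If the categories also carried the drug name, no category would be shared and separation would be complete by construction.

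The last row is harmless because the flag was generated independently of treatment given the covariates.

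**Step 4: effect on the standard error.** A second simulation used one mg scale: 120 cohorts of 9000, hazard ratio 0.83, 12% per year, up to 2 years, and a Poisson model on treatment, age and score. The standard error of the log hazard ratio was 0.053 without dose, 0.132 with mg and 0.127 with log mg. The ratios are 0.132/0.053 = 2.5 and 0.127/0.053 = 2.4. This shows the direction under one coding family only.

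**The case against.** Several points on the other side are fair.

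- **Dose is a candidate.** The list names variables to be considered, and the score is still to be built. A reader might infer that the score separates the arms and that the primary comparison loses its overlap. The article does not support that. It supports only that this could happen if dose is retained on an absolute scale. On the other hand, nothing in the section would remove dose, and selection by prediction of treatment would favour it.
- **Coding is unstated.** The loss runs from total to almost none. Analysis plan refers details to an online appendix that is not shown, so the lack of a coding in the article is no evidence that a harmful one was planned.
- **Index dose is recorded at the index date.** It is therefore baseline in the calendar sense. This does not rescue it: it is decided together with the drug and has meaning only given the drug.
- **Power collapse.** A reader might take the second simulation to mean that power falls from 90% to 23%, its simulated rejection rates. Those rates should not be relied on. They rest on mg values outside the documents and on 120 replicates. With |ln 0.83| = 0.186, the reported standard errors imply Φ(0.186/0.053 − 1.96) ≈ 94% and Φ(0.186/0.132 − 1.96) ≈ 29%.
- **Method of adjustment.** The primary analysis adjusts by age, sex and score; Analysis plan reserves inverse-probability weighting for the as-treated analysis. A claim about collapsing weights would therefore not fit the primary estimate. Complete separation would also show when the score is fitted, before any outcome is analysed. Bias was not quantified.

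Dose as an effect modifier in Analysis plan is a different use and does not justify its place in the score. What stands is that the list includes a variable that fails the section's own criterion.

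**Conclusion.** The point holds in a limited form and should be fixed. Listing the index anticoagulant dose as a baseline predictor of which anticoagulant was given is wrong under any coding; that conclusion rests on the text alone.

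The size of the damage is conditional on two things the article does not settle: whether dose is retained, and how it is coded. On an absolute scale, with the assumed inputs above, overlap ranges from none to 59% of patients, and the standard error can be expected to rise materially. With flag coding the loss is small or negligible. The documents do not support saying that the primary analysis as planned lacks overlap, or attaching a particular loss of power to it.

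**What to change.** Delete dose from the predictor list in Control for confounding. Add one sentence: the conventional and high-dimensional scores use only variables fixed before the index dispensing, and attributes of the index prescription (dose, strength, quantity, days supplied) are excluded, including from the empirical selection of medication variables. Keep the patient factors already collected that drive dose choice, such as age and renal function, so that no confounding information is lost.

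The cost is one deleted word, one added sentence and a check that the covariate window for the high-dimensional score closes before the index dispensing. No new data are needed and no clinical rule is affected.
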